### Statistical analysis

The analysis of efficacy endpoints will be conducted on an intention-to-treat basis. The primary endpoint was the incidence of SAP within 7 days postrandomization. To assess the difference in SAP incidence between the two groups (RIC group vs. Sham-RIC group), we used a modified Poisson regression model to analyze the primary efficacy endpoint. Adjustments for stratification factors, including age, sex, and NIHSS score, were incorporated into the model to control for potential confounding effects.

For secondary endpoints, continuous variables will be analyzed via linear regression models, with the same adjustments applied for stratification factors. Binary variables are analyzed via modified Poisson regression, whereas ordinal variables are analyzed via ordinal regression models. Time-to-event variables will be evaluated via Cox proportional hazards regression, with stratification factors controlled throughout.

Missing data for the primary endpoint will be addressed using multiple imputation methods to minimize potential bias. For secondary endpoints, no imputation will be applied. Given the exploratory nature of these outcomes, analyses will be limited to participants with complete data only.

Adverse events will be documented and reported. Statistical significance will be defined as a *P* value < 0.05. This study did not set an interim analysis.

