**Inclusion criteria**
• Age ≥ 18 years old
• Diagnosis of acute ischemic stroke
• RIC or Sham-RIC can be treated within 24 h after stroke onset
• NIHSS score ≥ 4
• Subject or his or her legally authorized representative was able to provide informed consent

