### Randomization

Randomization will occur after written informed consent is obtained from the patient or his or her guardian. Following successful screening of participants, patients will be randomly assigned to either the RIC group or the Sham-RIC group at a 1:1 ratio via randomized blocks (4, 6, and 8) stratified by age (≤ 70 or > 70 years old), stroke severity (NIHSS scores between 4 and 20 years or higher than 20), and sex (male or female). A central network randomization system will generate random code. Neither patients nor researchers will have information on the group allocation. Both RIC and Sham-RIC will be administered via equipment with the same appearance but with different pressure settings for the two treatment regimens. Additionally, consecutive enrolled subjects will not be placed in the same ward for this study.

At the end of this study, the subjects were asked several questions, as shown in Table 2, to investigate unblinding situations. Unblinding will only be allowed if a participant’s health is at risk and the attending physician deems it necessary. Unblinding must be approved by the principal investigator and documented.

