### Baseline measurements

In addition to confirming eligibility for AIS, a comprehensive baseline assessment will be conducted prior to randomization. This assessment will encompass several key variables, including demographic characteristics, clinical and medical history, physical examination findings, vital signs, smoking and alcohol consumption status, and medication usage within 1 week prior to admission. Additionally, laboratory examinations, neuroimaging, and chest imaging, including CT or chest X-ray scans, will also be performed. Furthermore, the assessment will utilize standardized scales such as the National Institutes of Health Stroke Scale (NIHSS), the modified Rankin scale (mRS), the self-rating depression scale (SDS), the generalized anxiety disorder scale (GAD-7), and a swallowing function assessment.

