### Outcomes

The primary efficacy endpoint is the incidence of SAP within 7 days of intervention after randomization. The details of the SAP diagnostic criteria [13] are presented in Table 4. The secondary endpoints were as follows: diagnosis of pneumonia by clinical doctors within 7 days; diagnosis of pneumonia by clinical doctors between 8 and 90 days; mRS score of 0–1 ratio on day 90; mRS score of 0–2 ratio on day 90; distribution of mRS scores on day 90; EuroQoL 5-Dimensions 5-Level questionnaire (EQ-5D-5L) score on day 90; NIHSS scores at 24 h after onset; NIHSS scores at day 7; incidence of urinary tract infection within 7 days; incidence of all infections within 7 days; all-cause mortality within 90 days; and total inpatient days. The incidence of adverse events was recorded and reported.

**Table 4 Tab4:** Suggested diagnostic criteria for definite and probable SAP in non-ventilated patients, based on CDC guidelines

At least one of the following criteria:
1. Fever (beyond 38 °C) with no other recognized cause
2. Leukopenia (lower than 4000 WBC/mm^3^) or leukocytosis (beyond 12,000 WBC/mm^3^)
3. For adults aged beyond 70 years, altered mental status with no other recognized causeAnd at least two of the following symptoms need to be observed:New onset of purulent sputum, a change in sputum character over 24 h, or increased respiratory secretions, or increased suctioning requirementsNew onset or worsening cough, dyspnea, or tachypnea (respiratory rate > 25/min) rales, crackles, or bronchial breath soundsWorsening gas exchange (e.g., O_2_ desaturation such as PaO_2_/FiO_2_ lower than 240, or increased oxygen requirements)And at least two serial chest radiographs must show at least one of the following:New or progressive and persistent infiltrate, consolidation, or cavitationOne definitive chest radiograph is acceptable in patients without underlying pulmonary or cardiac disease

Legend: Definite SAP: all CDC criteria are fulfilled, including diagnostic changes on at least one chest x-ray. CDC refers to the Centers for Disease Control and Prevention; *FiO*_*2*_ Fraction of inspired oxygen, *PaO*_*2*_ Partial pressure of oxygen, *SAP* Stroke-associated pneumonia, and *WBC* White blood cell count

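### Read literally, the models adjust NIHSS at 24 h and day 7 for baseline severity only through the 4–20 versus >20 split; naming the continuous baseline score as a covariate would recover precision

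*Protocol article*

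**What the plan says.** All references are to the protocol article.

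- **Covariates, primary model** (Statistical analysis): "Adjustments for stratification factors, including age, sex, and NIHSS score, were incorporated into the model".
- **Covariates, continuous secondary endpoints** (same section): "continuous variables will be analyzed via linear regression models, with the same adjustments applied for stratification factors". The paragraph closes by saying that the stratification factors are controlled throughout.
- **Definition of the factors** (Randomization): allocation is "stratified by age (≤ 70 or > 70 years old", by severity as "NIHSS scores between 4 and 20 years or higher than 20" (the word for years is plainly a slip), and by sex. Each factor has two levels.
- **Endpoints concerned** (Outcomes): "NIHSS scores at 24 h after onset; NIHSS scores at day 7" are two of the secondary endpoints. The Statistical analysis section calls the secondary outcomes exploratory.
- **Baseline data** (Baseline measurements): the assessment before randomisation uses "standardized scales such as the National Institutes of Health Stroke Scale (NIHSS" and other scales, so every patient should have an exact baseline score. Eligibility requires "NIHSS score ≥ 4".

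The article does not say whether age and NIHSS enter the models as the randomisation categories or as measured values.

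**The concern.** The covariates are introduced as stratification factors, and the only definition of those factors is the two-level one. On that reading, a patient who starts at NIHSS 4 and one who starts at 20 have the same severity covariate when day 7 NIHSS is analysed. Most of the variation in baseline severity may well lie inside that band.

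When the outcome is a later value of a scale measured at baseline, the baseline value is usually the strongest predictor of it. A linear model that includes it removes that variation from the residual and also corrects for chance imbalance within the wide lower band. A model with only the split leaves much of that variation in the standard error. What is at stake is wider confidence intervals for two reported endpoints than the collected data require. Treatment is randomised, so neither version biases the estimated effect.

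**Working it through.** **1. The plan's own figure.** The Sample size section gives 1486 patients for 17.0% versus 11.9%, 80% power, two-sided 0.05. With unpooled variance:

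n per arm = (1.960 + 0.842)² × (0.17×0.83 + 0.119×0.881) / 0.051² = 7.849 × 0.2459 / 0.002601 ≈ 742.2, rounded up to 743, so 1486 in total.

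The figure reproduces exactly (the pooled-variance formula gives 1490). No covariate enters it, so covariate coding does not affect it.

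**2. Formula for the NIHSS endpoints.** Let r be the correlation between baseline and day 7 NIHSS, and k the correlation between the baseline score and the indicator for a score above 20. If day 7 NIHSS is linear in the baseline score, the residual variance as a share of the total is:

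- continuous baseline: 1 − r²
- indicator only: 1 − (r·k)²

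The variance of the treatment effect changes by the ratio (1 − r²) / (1 − (r·k)²).

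**3. Inputs.** From the article: the cut at 20 and the lower limit of 4. **Assumed**, because the article gives neither: r from 0.5 to 0.8, and four baseline distributions (4 plus a gamma variable, rounded, capped at 42).

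**4. Results: variance with the continuous score divided by variance with the split only.**

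| Assumed median NIHSS | Share above 20 | k² | r = 0.5 | r = 0.6 | r = 0.7 | r = 0.8 |
|---|---|---|---|---|---|---|
| 7 | 1.6% | 0.278 | 0.806 | 0.711 | 0.590 | 0.438 |
| 8 | 5.4% | 0.465 | 0.849 | 0.769 | 0.661 | 0.513 |
| 10 | 10.3% | 0.563 | 0.873 | 0.803 | 0.704 | 0.563 |
| 12 | 15.9% | 0.613 | 0.886 | 0.821 | 0.729 | 0.592 |

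Worked cell (median 7, r = 0.7): (1 − 0.49) / (1 − 0.49×0.278) = 0.510 / 0.864 = 0.590.

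- The split carries about 28–61% of the variance of the baseline score.
- Variance falls by 11% (1 − 0.886) to 56% (1 − 0.438) over the whole table, and by 27–41% at r = 0.7.
- The standard error falls by about 6–10% at r = 0.5, 15–23% at r = 0.7 and 23–34% at r = 0.8.
- At r = 0.7, 1650 × 0.590 ≈ 974 to 1650 × 0.729 ≈ 1202 patients analysed with the continuous score match the precision of 1650 analysed with the split.

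**5. Check with another shape.** A truncated log-normal on 4–35 (4.5% or 10.4% above 20) gives k = 0.66 or 0.745. The inverse ratio, split over continuous, is then 1.32 or 1.25 at r = 0.6, 1.54 or 1.43 at r = 0.7, and 2.00 or 1.79 at r = 0.8. At r = 0.7 this is a cut of 1 − 1/1.54 = 35% or 1 − 1/1.43 = 30%, inside the range above.

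The same formula applies to NIHSS at 24 h, but no figure was computed for that endpoint.

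**6. Primary endpoint, for comparison.** Modified Poisson regression was simulated with N = 1650, 17% SAP in controls, a risk ratio of 0.70, and assumed odds ratios of 1.10–1.20 per NIHSS point and 1.4–1.6 per decade of age, 1500 runs per scenario. The mean standard error of the log risk ratio, strata versus continuous covariates, was 0.1204 vs 0.1190, 0.1188 vs 0.1162 and 0.1167 vs 0.1128: a fall of 1.2%, 2.2% and 3.3%. Power was 84.0 vs 84.9%, 85.1 vs 87.1% and 87.1 vs 88.5%.

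**The case against.** **The coding is not stated.** The primary-model sentence names the NIHSS score, not a severity stratum. Continuous age and NIHSS are therefore a possible reading, under which nothing is lost. Coding of covariates is also often settled in an analysis plan, which is not shown here. This stands as a limit on the finding. It does not remove it: the covariates are described as stratification factors, the only definition of these is categorical, and no baseline-score term is named for the NIHSS endpoints. The proposed sentence helps on one reading and does no harm on the other.

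**Adjusting for the stratification factors is standard and valid.** True. There is no bias and no problem with type I error, and the secondary outcomes are labelled exploratory. The point concerns efficiency only.

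**Stronger readings that the article does not support:**

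- A reader might infer that day 7 NIHSS is not adjusted for baseline at all. Even on the categorical reading it is adjusted in part, through the split.
- A reader might infer that the primary SAP analysis is materially weakened. The simulated gain is only 1–3% in standard error, and power is above the 80% target under either coding.
- A reader might infer that the multiple imputation is restricted to the same categories. The article lists no imputation covariates, so there is nothing to criticise.
- A reader might want swallowing function added because it is measured at baseline. Nothing in the article makes its absence from the models an error, and adding it after recruitment has ended is a debatable change.

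**Timing.** The Intervention and assessment section reports that recruitment was completed in September 2024, so a change to the covariates is late. This stands, and the fix allows for it.

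**Conclusion.** The point holds as a precision issue for two secondary endpoints, NIHSS at 24 h and at day 7. On the natural reading of the article, each is adjusted for its own baseline only through the 4–20 versus >20 split, while the exact score is available. For day 7 NIHSS, the continuous score would cut the variance of the treatment effect by about 11–56% for correlations of 0.5–0.8, and by about 27–41% at 0.7.

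These figures rest on an assumed correlation, assumed baseline distributions and a linear relation between the two scores. The gain is zero if the continuous score is already intended. The validity of the trial, the sample size of 1486 and the primary conclusion are not in question.

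**What to change.** Add one sentence to the analysis section, before unblinding: the linear models for NIHSS at 24 h and at day 7 include baseline NIHSS as a continuous covariate in addition to the stratification factors, and the model with the stratification factors alone is a sensitivity analysis. If the continuous score was already intended, the same sentence makes that explicit.

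If unblinding has occurred, keep the planned model as the main analysis and report the continuous-baseline model as supplementary, labelled as such.

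Continuous NIHSS and age in the primary SAP model are optional. The expected gain is small, and a late change to the primary model has its own cost in prespecification.

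No new data are needed, since the score is collected before randomisation. The cost is the sentence and one extra model for each of the two endpoints.

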### Study organization

An independent data monitoring committee is responsible for regularly monitoring patient safety, treatment efficacy, and overall study progress and for assessing whether early termination or protocol amendments are necessary.

## Discussion

In our previous pilot clinical trial investigating the safety and efficacy of remote ischemic conditioning for SAP, 19 patients with AIS onset within 48 h were randomly assigned to the RIC group (six consecutive days, twice daily), whereas 22 patients were assigned to the control group. The results of this study showed that RIC was safe among patients with AIS. Although the difference was not statistically significant in either univariate or multivariate analyses, the incidence of SAP was lower in the RIC group (10.5%) than in the control group (27.3%) [15]. The lack of statistical significance may be attributed to the small sample size, limiting the power to detect differences between groups, and recent evidence suggests that the peak of apoptosis and immune suppression following stroke may occur within the first 24 h [16], indicating that earlier prevention might be more beneficial among these patients. Therefore, we aimed to conduct a fully powered clinical trial with adjusted inclusion and exclusion criteria to investigate the efficacy of RIC in preventing SAP in AIS patients within 24 h of symptom onset following randomization. We hypothesize that 7 days of RIC will reduce the relative risk of SAP by 30%.

We implemented several adjustments to address the limitations identified in the previous study [15]. The inclusion criteria were refined to ensure that the treatment window was within 24 h of stroke onset, as this period is critical for effectively reducing apoptosis and modulating immune responses. Since the sample size calculation was based on previous studies [14], clinical expertise, and prior surveys on SAP incidence at Xuanwu Hospital of Capital Medical University and our participant selection criteria are relatively broad, we anticipate few practical challenges in recruiting a sufficient number of patients. An important advantage of our approach is that the results of our trial can be generalized to a wider population of stroke patients. Additionally, at the end of the study, we used a method from previous research [17] and contacted the participants, asking them about their knowledge of group allocation by answering the questions in Table 1. This upcoming trial is anticipated to conclude in the second quarter of 2025.

Owing to the low cost and ease of use of RIC devices, this intervention has strong potential for widespread adoption by patients and healthcare providers. If successful, this study could demonstrate that RIC significantly reduces the incidence of SAP, promotes recovery, and ultimately improves the quality of life for a large population of stroke patients.

## Trial status

The participant recruitment for this trial commenced on January 22, 2024, and is anticipated to conclude by the end of December 2024. This protocol is the third version, version date: July 19, 2023.

## Summary and conclusions

RIC is a convenient and noninvasive intervention, and the RICA-2 trial aims to investigate whether RIC treatment can effectively reduce stroke-associated pneumonia while also identifying any potential safety concerns.
